### Study schedule

The detailed measurements that will be assessed at every visit are described in Table 3.

**Table 3 Tab3:** A brief study schedule at every visit

	On admission	Visit 1 (1 month)	Visit 2 (3 months)
Informed consent form	*		
Recording demographic data	*		
Medical history taking	*		
Physical examination^a^	*	*	*
Blood pressure	*	*	*
FBS	*	*	*
ALT	*	*	*
Lipid profile	*		*
Drug chart	*	*	*
FFQ	*	*	*
IPAQ-SF	*	*	*

*Abbreviations: ALT* Alanine aminotransferase, *FBS* Fasting blood sugar, *FFQ* Food frequency questionnaire, *IPAQ-SF* International Physical Activity Questionnaire–Short Form

^a^ Body weight, height, waist circumference, and hip circumference

* performing given activity/investigation in that perticular visits

### Measurement tools

#### Anthropometric measurements

Anthropometric measurements will be performed using calibrated equipment by a research assistant adhering to the WHO guidelines [29]. Height will be taken to the nearest 0.1 cm, as the maximum distance to the uppermost position on the head from the heels, with the individual standing barefoot and in full inspiration using a standard stadiometer (Seca 823; Seca, Hamburg, Germany). Body weight will be measured to the nearest 0.1 kg using an electronic weighing scale (Seca 803) with the participants wearing light indoor clothing. BMI will be calculated as weight in kilograms divided by height squared in meters (kg/m^2^). WC will be measured midway between the iliac crest and the lower rib margin at the end of normal expiration using a plastic, nonelastic flexible tape to the nearest 0.1 cm. Hip circumference will be measured at the widest level over the greater trochanters using a plastic flexible tape to the nearest 0.1 cm. Seated BP will be measured after at least a 10-minute rest using a mercury sphygmomanometer (model 0125; Accoson, Harlow, UK).

#### Dietary measurements

A validated FFQ will be used as an interviewer-administered questionnaire by a trained research assistant to obtain habitual intake of calories as well as macro- and micronutrients. Data will be analyzed using NutriSurvey 2007 software (EBISpro Software, Willstätt-Legelshurst, Germany).

### Statistical analysis

Completed questionnaires will be checked before data entry. Data will be entered and analyzed using IBM SPSS Statistics version 21.0 statistical software (IBM, Armonk, NY, USA). One-sample Kolmogorov-Smirnov analysis will be used to test the distribution of variables. Characteristics of patients will be examined by chi-square tests for categorical variables and by Student’s *t* test and analysis of variance for continuous variables. Chi-square tests for independence will be used to compare weight changes between different BMI categories. Associations between biochemical parameters will be tested by Pearson’s correlation coefficient for normally distributed variables and Spearman’s correlation coefficient for variables that are not normally distributed. Statistical significance will be set at *p* < 0.05.

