### Sample size

The sample size will be selected on the basis of a pilot survey, and the number needed for recruitment will be determined to account for a confidence level of 95%, a confidence interval of 10%, and 80% statistical power. A 10% hypothesized difference of participants’ body weight between the control and intervention groups following the plate model diet at the end of 12 weeks is taken as the primary outcome when calculating the sample size. Because the other biochemical parameters (BP, lipid profile, fasting blood sugar [FBS], and ALT) are prone to vary with medication and compliance with medication, they were not regarded in sample size calculations. A subsequent 5% withdrawal rate and another 15% loss to follow-up (total of 20%) are accounted for in the calculation. A total sample of 120 will be recruited over an anticipated period of 3 months.

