### Outcomes

The primary outcome is mean body weight reduction of 10% in the test group following the plate model diet for a period of 12 weeks compared with the control group. The following secondary outcomes will be evaluated in the test group compared with the control group at the end of the completion of the 12-week period from commencement of intervention: reduction of systolic and diastolic blood pressure, BMI, waist circumference (WC), hip circumference, waist-to-hip ratio, FBS, serum total and LDL cholesterol, serum ALT, and total caloric intake/day (FFQ), as well as improvement in level of physical activity (based on IPAQ-SF) and mean increment in serum HDL cholesterol level.

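### The only test assigned to weight change is a chi-square across BMI categories, which leaves out the allocated arm and cannot test the between-arm primary outcome

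*Protocol article*

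**What the plan says.** All references are to the protocol article.

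- **Outcomes:** the definition reads "The primary outcome is mean body weight reduction of 10% in the test group"; it is set at 12 weeks and judged against control. The Objectives and hypothesis section states the same expectation.
- **Sample size:** the calculation is said to rest on a hypothesised 10% between-arm difference in weight at 12 weeks.
- **Anthropometric measurements:** "Body weight will be measured to the nearest 0.1 kg using an electronic weighing scale".
- **Statistical analysis, weight change:** "Chi-square tests for independence will be used to compare weight changes between different BMI categories".
- **Statistical analysis, other tests:** patient characteristics are to be examined with chi-square tests if categorical, and with Student's t test and ANOVA if continuous. For correlations the text says "Associations between biochemical parameters will be tested by Pearson’s correlation coefficient for normally distributed variables", with Spearman's coefficient otherwise.

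No sentence in the Statistical analysis section mentions the test or control group, and no other section names a test for the primary outcome. The Randomization section says that subjects are stratified by sex. The Study schedule table has body weight measured on admission, at 1 month and at 3 months.

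**The concern.** The outcome and its stated test differ in two ways. The outcome contrasts two arms, whereas the test contrasts BMI categories. The outcome is a mean of a continuous measurement, whereas the test needs counts in classes, and no cut-points for weight change are given. The BMI categories are also undefined, and the text does not say whether baseline or 12-week BMI is meant.

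The stake is the primary result. An analyst who takes the weight-change sentence at face value would report a p-value that says nothing about the plate model. An analyst who looks elsewhere in the section finds a t test tied to patient characteristics. The form of the primary comparison could then be settled after the data are seen.

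**Working it through.** **1. Outcome and tests side by side**

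| Item | Compared groups | Scale |
|---|---|---|
| Primary outcome (Outcomes, Sample size) | test vs control | mean, continuous |
| Chi-square (the only test naming weight change) | BMI categories | classes, cut-points not given |
| t test, ANOVA | not stated; patient characteristics | continuous |
| Pearson, Spearman | none; biochemical parameters | continuous or ranked |

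No row of tests matches the first row on groups, scale and variable together.

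**2. Inputs for a numerical check**

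- From the protocol: 120 recruited, 20% lost, alternating allocation (about 1:1), significance at 0.05 (taken as two-sided). Evaluable: 120 × 0.80 = 96, or 48 per arm.
- The protocol gives no SD, so the figure of 120 cannot be reproduced for a comparison of means. This point does not depend on it.
- Assumed: SD of percentage weight loss 5 points, mean loss 2% in controls, weight loss classed at 5%, three equally likely BMI categories unrelated to arm or to weight loss.

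**3. What the chi-square by BMI category sees**

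The chance of losing at least 5% is 1 − Φ((5 − mean)/5).

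- Control (mean 2): 1 − Φ(0.6) = 0.274.
- Test arm, 3-point effect (mean 5): 1 − Φ(0) = 0.500.
- Test arm, 10-point effect (mean 12): 1 − Φ(−1.4) = 0.919.

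Each BMI category contains both arms in about equal numbers, so the expected proportion is the same in every category:

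- 3-point effect: (0.274 + 0.500)/2 = 0.387.
- 10-point effect: (0.274 + 0.919)/2 = 0.597.

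The null hypothesis of this test is therefore true whatever the treatment does. The effect moves all rows together, and the test cannot detect it.

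**4. Simulation (4,000 runs, same inputs)**

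| True arm difference | Chi-square by BMI category rejects | t test between arms rejects |
|---|---|---|
| 0 points | 5.1% | 5.1% |
| 3 points | 4.9% | 83% |
| 10 points | 4.7% | 100% |

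The chi-square column stays at the significance level, within simulation error (standard error √(0.05 × 0.95/4000) = 0.34 points). The formula power of the arm comparison at 3/5 = 0.6 SD is 83.6%, in line with the simulated 83%.

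**5. How much the choice of continuous model matters**

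For a given SD and baseline-to-12-week correlation r, the detectable difference with a change score exceeds that with ANCOVA by the factor √(2(1 − r)/(1 − r²)) = √(2/(1 + r)). With assumed r of 0.90, 0.95 and 0.97 this is 1.026, 1.013 and 1.008. The gain from ANCOVA over a change score is only about 1% to 3%. What matters is that the arms are compared on a continuous scale.

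**The case against.** **The sentence may be only a subgroup description.** Nothing labels it the primary analysis. If it is an extra description, what remains is that no primary test is named, and a condensed article may leave that to an analysis plan not shown here. The first part stands and limits the severity. But the protocol is not silent on weight change: it assigns it a test. Even as a description, that test discards the continuous scale and leaves out the arm.

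**A two-group test for continuous variables is present.** The t test sentence immediately precedes the chi-square sentence, and the design has only two groups. This shows that an arm comparison may well be intended. It does not settle the matter, because the sentence is worded for patient characteristics and names neither weight change nor the arms.

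**Stronger readings that the document does not support:**

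- *The trial will yield no treatment effect or confidence interval.* That would follow only if the chi-square sentence were the whole analysis of weight, which the text does not say.
- *Power will be lost through a chi-square between arms.* No such test is stated. Even if one were used, the loss would be small at the protocol's own 10-point difference unless weight change were very variable: with an assumed control loss of 2% and cuts at 5% or 10%, power is above 99.9% at SD 4, about 97% at SD 10, and near 60% only at SD 17.5.
- *Unadjusted 12-week weights will be compared, at a large cost in precision.* The outcome is defined as a reduction and the Discussion speaks of weight reduction over time, so a change score is the fair comparator.
- *Normality testing decides the between-arm test.* The text says "One-sample Kolmogorov-Smirnov analysis will be used to test the distribution of variables", but normality is given a stated role only in choosing between the two correlation coefficients.

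**Conclusion.** The point holds in a limited form. The single test that the protocol assigns to weight change cannot test the primary outcome, because it leaves out the arm and needs a continuous variable to be categorised. The t test and analysis of variance sentence leaves the arm comparison ambiguous at best.

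The mismatch rests on the text alone. The size depends on assumptions: if BMI category is unrelated to arm, the stated test rejects at about 5% whatever the treatment effect. If 12-week BMI were meant, the categories would themselves be affected by treatment, and the test would still give no arm difference.

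This should be fixed before analysis. It is not fatal, because the sentence is not declared primary and the data needed for the right comparison are already being collected.

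**What to change.** Replace the chi-square sentence with: *The primary analysis compares 12-week body weight between allocated arms by ANCOVA adjusted for baseline weight and sex (the stratification factor), reported as the adjusted mean difference with 95% CI.*

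Keep BMI category only as a secondary, exploratory analysis of arm by baseline BMI, with weight change kept continuous. State that the existing t test and chi-square sentence describes patient characteristics, if that is what is meant.

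The cost is a dated amendment to the analysis wording. The trial status is given as recruiting, so the amendment should be made before analysis starts. Baseline weight, 12-week weight and sex are already recorded, so no new data are needed and the sample size is unchanged.

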## Methods/design

### Objectives and hypothesis

The aim of the present study is to evaluate the effects of a plate model on modification of selected cardiometabolic risk factors in patients with a history of MI. Our hypothesis is that intake of a healthy diet using the model plate will improve coronary risk factors with an expected mean weight reduction by 10% in the test group after adopting the plate model diet for a period of 12 weeks and reduction of total cholesterol, LDL cholesterol, total cholesterol/high-density lipoprotein (HDL) ratio, blood pressure (BP), and alanine aminotransferase (ALT) compared with the control group.

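### The statistical section does not state the between-arm comparison at 12 weeks that the laboratory outcomes call for; naming one, adjusted for baseline and sex, would cost almost nothing

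*Protocol article*

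**What the plan says.** Under Objectives and hypothesis, the expected benefits include "reduction of total cholesterol, LDL cholesterol, total cholesterol/high-density lipoprotein (HDL) ratio". The same sentence goes on to the other markers and closes with the comparator: "blood pressure (BP), and alanine aminotransferase (ALT) compared with the control group". Under Outcomes, the article states "The following secondary outcomes will be evaluated in the test group compared with the control group at the end of the completion", and it places that point at 12 weeks. The list that follows includes fasting blood sugar, total and LDL cholesterol, ALT and HDL cholesterol. Together the two sections fix the contrast (test against control) and the time point (12 weeks). The total cholesterol/HDL ratio appears only in the hypothesis, but it follows from the lipid profile.

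The Statistical analysis section names three kinds of test:

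- For the description of the patients, the article writes "Characteristics of patients will be examined by chi-square tests for categorical variables and by Student’s *t* test and analysis of variance for continuous variables".
- For weight, the grouping is by baseline size and not by arm: "Chi-square tests for independence will be used to compare weight changes between different BMI categories".
- For the laboratory markers, the only sentence is "Associations between biochemical parameters will be tested by Pearson’s correlation coefficient for normally distributed variables", and Spearman's coefficient is the alternative where normality fails.

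The section closes with one threshold for all of these: "Statistical significance will be set at *p* < 0.05". No sentence in it mentions the arms, the control group or a comparison of any outcome between groups.

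**The concern.** The laboratory markers are part of the study hypothesis, and the question about them is whether they differ by arm. The one sentence in the statistical section that names them answers another question: whether two markers move together. Its null hypothesis is zero correlation between two laboratory values, and allocation plays no part in it.

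The sentence that could supply an arm comparison has patient characteristics as its subject and names no outcome, time point or arm. An analyst working from this text has to infer the test of the secondary hypothesis. The likeliest inference, a plain t test on the 12-week values, leaves the baseline measurement unused. There is also a risk in reporting: significant marker-to-marker correlations could be presented beside the trial's results and taken as support for the diet.

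**Working it through.** **Matching sections.** The article gives no figure on this point to reproduce, so the first step is to set each named test against the question in Outcomes.

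| Test named | Variables named | Arm named? | 12 weeks named? |
|---|---|---|---|
| Chi-square, t test, analysis of variance | Patient characteristics | No | No |
| Chi-square for independence | Weight change, across BMI categories | No | No |
| Pearson or Spearman correlation | Biochemical parameters, with one another | No | No |

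**Could the correlations stand in for an arm comparison?** Inputs: total sample 120 with 20% withdrawal and loss (Sample size section), so 120 × 0.8 = 96 evaluable; alternating allocation (Randomization section), so 48 per arm; significance level 0.05, taken as two-sided because the article does not say. The correlations between markers are assumed, since none is given.

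By Fisher's z, the chance of a significant correlation is approximately Φ(atanh(r) × √(96 − 3) − 1.96), plus a negligible opposite tail, with √93 = 9.64:

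- r = 0.1: 0.100 × 9.64 = 0.97, giving 16%
- r = 0.2: 0.203 × 9.64 = 1.96, giving 50%
- r = 0.3: 0.310 × 9.64 = 2.98, giving 85%
- r = 0.5: 0.549 × 9.64 = 5.30, giving about 100%

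None of these depends on whether the diet works.

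A simulation (4,000 runs, two normal markers, arms pooled, the same shift in both markers) sets the correlation test beside a two-sample t test by arm. Entries are the proportion significant:

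| Correlation | Diet effect | Correlation test | t test by arm |
|---|---|---|---|
| 0 | none | 5% | 5% |
| 0 | 0.58 SD | 11% | 80% |
| 0.3 | none | 85% | 4% |
| 0.3 | 0.58 SD | 96% | 80% |
| 0.5 | none | about 100% | 5% |
| 0.5 | 0.58 SD | about 100% | 79% |

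The correlation test responds to how the markers relate to each other. It misses a real effect on unrelated markers and is almost always significant on related ones. Total cholesterol contains LDL and HDL, so some of these correlations will be present in any case.

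**What would baseline adjustment add to a plain t test?** With 48 per arm, the smallest difference detectable with 80% power is (1.960 + 0.842) × √(2/48) = 0.57 SD. Adjusting for baseline multiplies this by about √(1 − ρ²), where ρ is the correlation between the baseline and 12-week values. The article does not give ρ, so a range is shown:

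- ρ = 0.3: 0.572 × 0.954 = 0.55 SD
- ρ = 0.5: 0.572 × 0.866 = 0.50 SD
- ρ = 0.7: 0.572 × 0.714 = 0.41 SD

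The Sample size section warns that these markers vary with medication, so the lower end is possible.

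**The case against.** Correlation is the right tool for asking how markers relate to one another, and nothing in the article says the correlations will test the hypothesis or count as evidence of a diet effect. This stands. A reader might infer from the statistical section that the correlations are the planned test of the laboratory outcomes, and that the plan therefore carries a 50% to 100% false-positive rate. The documents do not support that. Those percentages are correct rejections of the correlation test's own null hypothesis. They would mislead only if a correlation were reported as a treatment effect, which no section proposes.

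The t test and analysis of variance for continuous variables can also plausibly be read as the arm comparison: the trial has two arms, the markers are continuous, and Outcomes already fixes the contrast and the time. This stands as a possible reading. It would give a valid, though unadjusted, comparison, so it cannot be said that the plan has no test for these outcomes. It does have to be inferred, from a sentence whose stated subject is patient characteristics.

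The simulation pools the arms at a single time, and the article does not say whether the correlations are pooled or computed within arm, or on which values. Correlations within arm would not compare the arms either, so the reasoning does not depend on this detail.

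Finally, the choice of model for each secondary outcome is commonly left to a fuller analysis plan, which may exist. Missing detail is therefore not the complaint. The point is that the tests the article does state do not line up with the contrast it states.

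**Conclusion.** The point holds as a misalignment that is easily corrected. Objectives and Outcomes pose a test-versus-control question at 12 weeks. The statistical section names the laboratory markers only in an analysis that ignores the arm, and it assigns its two-group tests to patient characteristics. Read strictly, it states no test of the laboratory part of the hypothesis. Read generously, it states a t test that leaves the baseline value unused. On either reading, a stated comparison by arm adjusted for baseline and sex is an improvement.

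For size: the rejection rates above show only that the correlations cannot serve as evidence of a diet effect. Baseline adjustment would lower the detectable difference from 0.57 SD to between 0.55 and 0.41 SD for assumed baseline correlations of 0.3 to 0.7. Both results assume 96 completers in equal arms and a two-sided 0.05 level. The mismatch between sections depends on none of these assumptions. These are secondary outcomes and the change is almost free, so this is an improvement to make rather than a flaw that invalidates the plan.

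**What to change.** In the Statistical analysis section, state that fasting blood sugar, total, LDL and HDL cholesterol, the total cholesterol/HDL ratio and ALT at 12 weeks will each be compared between the allocated arms by a linear model with arm, the baseline value and sex. Sex belongs in the model because the Randomization section stratifies on it. Use the log scale or a rank-based method for a skewed marker. Report the adjusted difference between arms with its 95% confidence interval. Label the Pearson and Spearman correlations as exploratory.

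The cost is a few lines of wording and slight extra analysis work. Table 3 already schedules fasting blood sugar, ALT and the lipid profile on admission and at 3 months, so no visit, sample or recruitment target changes.

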### Risks and benefits

The risks associated with the procedures will be negligible. The intervention is minor and expanded in a very mild manner compared with standard of care, but the expected benefits it would bring to individuals, the scientific community, and the health sector would be much higher. In case of any unlikely outcome such as unexpected weight loss or sudden deterioration of the disease condition of the patient, the intervention will be either discontinued or modified.

Investigation results will be sent to each subject under confidential cover. In the event that any abnormality is detected, subjects will be contacted by the investigators by phone and referred to relevant persons/institutes for further management according to their wish. Furthermore, for any clarifications during the study period, all the participants are provided with the contact information of the research assistant and the institute.

### Data collection

Data collection will be performed according to the hospital’s standard operating procedure by a research assistant.

### Monitoring and data management

Monitoring of data will be done on a weekly basis by the senior authors of the study (AP and RJ). All the data will be stored electronically in Excel spreadsheets (Microsoft, Redmond, WA, USA), and an SPSS database will be maintained and updated daily by a research assistant. Missing data and dropout will be stricken from the database and nullified. The sample size is calculated to compensate for missing data and dropouts throughout the study period.

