### Suspension criteria

Patients may be withdrawn from the study in the following circumstances:Subject demands to discontinue the studyUnusual changes in clinical test resultsPrincipal investigator’s decision to terminate the study (low rates of compliance, complications, or inability to sustain the study for various reasons)

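### Dropouts and missing data are deleted on the ground that the sample size was inflated, but inflation protects precision only and does not prevent selection bias in the primary comparison.

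*Protocol article*

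**What the plan says.** Under Monitoring and data management the protocol sets a rule: "Missing data and dropout will be stricken from the database and nullified". The next sentence gives the reason: "The sample size is calculated to compensate for missing data and dropouts throughout the study period".

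The Sample size section supplies the allowance: "A subsequent 5% withdrawal rate and another 15% loss to follow-up (total of 20%) are accounted for in the calculation". The total is fixed there at 120.

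The Suspension criteria open with "Patients may be withdrawn from the study in the following circumstances". Three grounds follow: the patient's own wish to stop, test results that change in an unusual way, and a decision of the principal investigator, explained in brackets as "low rates of compliance, complications, or inability to sustain the study for various reasons".

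Two further facts matter. Study materials lists the food diary among the materials of the intervention arm and says that it will be used to analyse compliance. Table 3 schedules body weight on admission, at 1 month and at 3 months.

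The article describes no all-randomised analysis set, no weighing after withdrawal, and no sensitivity analysis that would offset the deletion rule.

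**The concern.** The primary outcome compares weight reduction at 12 weeks between the two arms. If the patients who leave are removed, that becomes a comparison of completers. It is fair only if those who leave differ from those who stay by the same amount, and in the same proportion, in both arms. A larger sample does nothing to secure this; it makes a biased estimate more precise.

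The withdrawal grounds make equal loss hard to take for granted. Fasting blood sugar, lipids and liver enzyme are secondary outcomes, so withdrawal for unusual test results can depend on outcome. If low compliance is a ground for withdrawing a patient, the diary gives a means of detecting it that exists in the plate arm only. The plate arm would then keep its better adherers, and the effect would look larger than it is. If those who leave the plate arm had instead lost the most weight, a real effect would be partly hidden.

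Information already collected may also be thrown away: a patient who attends at 4 weeks and then drops out has a valid weight that the rule may remove.

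This is a stated rule, not a detail left to a later analysis plan, and no later plan can analyse records that have been removed from the database.

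**Working it through.** **1. The plan's own figures.** 5% + 15% = 20%. Of 120 patients, 0.20 × 120 = 24 are expected to be lost and 96 remain, or 48 of 60 per arm with equal loss. The document gives no SD for the weight comparison, so 120 cannot be re-derived as a two-arm sample size. That is a separate matter and does not affect this point.

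**2. What deletion does to the estimate.** Let d be the share lost in an arm and D the mean weight loss of completers minus that of dropouts. The completers' mean exceeds the full-arm mean by d × D, so

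bias = d₁D₁ − d₀D₀ (1 = plate, 0 = control).

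The sample size does not appear. The table assumes no true effect, an SD of 5 percentage points (assumed) and 60 per arm before loss:

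| Loss, plate / control | D₁ / D₀ (points) | Bias (points) | Type I error |
|---|---|---|---|
| 20% / 20% | 5 / 5 | 0.2×5 − 0.2×5 = 0 | 0.05 |
| 20% / 20% | 3 / 0 | 0.2×3 = +0.6 | 0.09 |
| 20% / 20% | 5 / 0 | 0.2×5 = +1.0 | 0.165 |
| 30% / 10% | 5 / 5 | 1.5 − 0.5 = +1.0 | 0.16 |
| 20% / 20% | −5 / 0 | −1.0 | 0.165 |

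The first row is the harmless case. The last shows that the sign can reverse.

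**3. Removal by compliance.** Assume a compliance score with correlation r to weight loss. The least compliant fraction q of the plate arm is removed, all other loss is random, and 48 per arm are analysed. For normal variables the expected bias in SD units is

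bias = r × φ(z_q) / (1 − q),

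where φ is the standard normal density and z_q its q-quantile. The multiplier is 0.109 at q = 5%, 0.195 at 10% and 0.350 at 20%. For example, 0.7 × 0.109 = 0.076 and 0.3 × 0.350 = 0.105. The standard error of the difference is about √(2/48) = 0.204 SD. Simulation with 60 per arm, no true effect and a two-sided t test at 0.05 gives:

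| Plate arm removed by compliance | Bias (SD), r = 0.3 to 0.7 | Type I error |
|---|---|---|
| 5% (3 of 60) | 0.03 to 0.08 | 5% to 7% |
| 10% (6 of 60) | 0.06 to 0.13 | 6% to 11% |
| 20% (12 of 60) | 0.10 to 0.24 | 8% to 24% |
| None (all loss random) | about 0 | 5% |
| 20% in both arms, same mechanism | about 0 | 5% to 7% |

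The first row uses the protocol's 5% withdrawal rate. The second is the case in which all six planned withdrawals (5% of 120) fall in the plate arm. The third needs every loss in the plate arm to be driven by compliance.

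**The case against.** The case for the plan does not defend the deletion rule. It limits what can be built on it.

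- **Size.** The protocol separates 5% withdrawal from 15% loss to follow-up. Removal for compliance belongs to the 5%, where the inflation of type I error is small. This stands. Loss to follow-up may also depend on outcome, but the document does not say so.
- **Asymmetry.** The Suspension criteria do not name the plate when they speak of compliance. Controls also receive dietary advice, and Table 3 schedules the food frequency questionnaire without restriction by arm. A reader might infer that compliance can be judged in the plate arm only; that goes too far. Because the diary belongs to the plate arm, unequal removal is plausible but not established.
- **Ambiguity.** Withdrawal is permitted, not required. The reference to low compliance follows wording about terminating the study, so it may describe stopping the trial and not removing a patient. Likewise, the missing data to be struck out may be single values or whole records. Dropouts are removed on either reading.
- **Not every route depends on outcome.** A patient's own request to stop has no stated link to weight.
- **Stopping for weight loss.** Risks and benefits says that in case of "unexpected weight loss or sudden deterioration of the disease condition of the patient, the intervention will be either discontinued or modified". A reader might infer that this conflicts with weight reduction as the primary outcome, or that such patients are deleted. Neither follows. It is a safety clause for an unlikely event in an individual, the outcome is an intended mean reduction, and the clause ends or changes the diet, not the patient's place in the data.

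**Conclusion.** The rule is wrong as written and should be changed before data are lost; the trial is already recruiting. That an inflated sample does not justify deleting dropouts holds without any assumption about the size of bias.

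The size and direction do depend on assumptions. With r between 0.3 and 0.7, random loss otherwise and 48 analysed per arm, bias runs from 0.03–0.08 SD at the protocol's own withdrawal rate to 0.10–0.24 SD if all 20% of plate-arm loss is compliance-driven. Type I error runs from 5–7% to 8–24%. Bias is near zero if loss is unrelated to outcome or the same in both arms. It would be tempting to quote 24% as the expected error rate, but that figure joins the strongest assumed correlation to a compliance removal rate four times the planned withdrawal rate. The document supports a risk of bias of uncertain size, not a known exaggeration of the effect.

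**What to change.** - Delete the sentence on striking out missing data and dropouts, together with the claim that the sample size compensates for them.
- State that all randomised patients stay in the database and are analysed in their allocated arm.
- State that weight is still measured at 4 and 12 weeks after the diet is stopped or modified, unless the patient withdraws consent to follow-up.
- Record low compliance as an adherence variable, not as a ground for exclusion from the analysis. Clarify whether the compliance wording in the Suspension criteria refers to a patient or to the whole study.
- Analyse with a method that uses the available 4-week weights, for example a mixed model for the 4- and 12-week weights with baseline weight and sex as covariates, and add a sensitivity analysis for missing 12-week weights. The particular model is a choice and can be set in the analysis plan.

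The cost is a change of wording, a few more weight measurements, modest analysis work, and possibly a smaller estimated effect.
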